### Adverse events

All adverse events that will occur during the study will be recorded. The records will include the description of these events, start time, severity and frequency of occurrence, end time, ongoing treatment, results, and the track and analysis.
A serious adverse event (SAE) is an adverse event in which any of the following circumstances can occur.
An event that causes the patient to die or endanger the patient’s life.The events that result in permanent or significant disability or loss of function in the patient.The events that lead to hospitalization.The important medical events need to use drugs or surgery to prevent serious consequences.Treatment of serious adverse events

Once a serious adverse event is found, the study physician must report to the study leader and the study team. The study team should report to the Ethics Committee and the responsible units within 24 h and record the serious adverse events in the original data. Original data may include carefully filling out the adverse event report form, recording the start time, the severity, the final outcome, the relationship with acupuncture treatment, the details of the treatment, and should immediately consult the relevant departments to take the necessary treatment.

The trial of a SAE patient will be discontinued and become a withdraw subject, while all costs for handling adverse events will be covered by this study.

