## Outcomes

The following outcomes will be assessed by independent outcome assessors. These assessors will be trained before participating in this trial and unaware of the group assignments. The outcome assessments will be performed at four time points including at the baseline, at the end of the stuck-moving needle acupuncture treatments, in the 4-week follow-up period, and at the end of the follow-up period.

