### Main outcome indicators

The primary evaluation index in the trial will be the change involved in the scores on the Visual Analogue Scale (VAS) and measurement of range of joint motion (ROM) from the baseline period through the 12 weeks of the follow-up period.

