### Statistical analysis

All statistical analysis will be carried out by the professionals using SPSS (v21.0) software. The participants in the statistical analysis will be unaware as well for the specific grouping content of the trial. This study will use a full analysis set (FAS) and per protocol set (PPS), and the final conclusion will be based on FAS. The full analysis set (FAS) is based on the intent to treatment (ITT). Patients who participate in randomization and receive at least one treatment will be included in the analysis. In the FAS analysis, for patients who do not complete the trial, the main indicators of the missing will be derived from the Last Observation Carried Forward (LOCF). Continuous variables will be presented as mean ± standard deviation (normally distributed data) or medians and ranges (non-normally distributed data). Frequencies and percentages will be used to count the data. All statistics will be performed by bilateral differential test, with *P* value < 0.05 considered statistically significant.

For the balance of basic values, analysis of variance or chi-square test or rank sum test will be used. For the primary and secondary outcome, the analysis of variance will be used. If confounding factors have an impact on the results, then the co-variance analysis will be used. For the safety analysis, the incidence of three groups of adverse events will be compared using a chi-square test, and the adverse events that will occur in this trial will be listed. At the same time, the paired *t* test will be used to compare the differences between the groups before and after treatment. The comparison among the three groups before and after treatment will be analyzed by variance. The rate changes before and after treatment in the three groups will be measured by chi-square test or non-parametric test.

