### Patient dropouts

Investigators will have the authority to terminate patient participation at any time if the investigator deems it is in the best interests of the patient. Termination criteria are as follows: (1) Patients with serious adverse reactions or combined with other critical illnesses in the study. (2) The subject asks to withdraw from the trial during the course of treatment and persuasion is ineffective. (3) Subjects who are not cooperating to the treatment and persuasion are ineffective by the doctor. (4) If the subject receives half of the treatment, then he or she should be included in the statistical analysis of efficacy.

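### The serious adverse event (SAE) rule ends trial participation rather than study treatment, so some obtainable VAS and ROM values are filled by LOCF; the effect is small and the repair cheap.

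*Protocol article*

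**What the plan says.** All places are in the protocol article.

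- **Adverse events.** The rule is "The trial of a SAE patient will be discontinued and become a withdraw subject". The same section counts hospitalization as serious, along with important medical events that need drugs or surgery. It also asks staff to document the event, "recording the start time, the severity, the final outcome, the relationship with acupuncture treatment" among the items, but the withdrawal sentence makes no use of relatedness.
- **Patient dropouts.** Investigators may end participation in the patient's interest. Criterion (1) is "Patients with serious adverse reactions or combined with other critical illnesses in the study". Criterion (4) is "If the subject receives half of the treatment, then he or she should be included in the statistical analysis of efficacy".
- **Outcomes.** "The outcome assessments will be performed at four time points including at the baseline, at the end of the stuck-moving needle acupuncture treatments", then at 4 weeks of follow-up and at its end. The Discussion places the 12 follow-up weeks after treatment ends.
- **Main outcome indicators.** The primary outcome is the change in VAS and ROM "from the baseline period through the 12 weeks of the follow-up period".
- **Statistical analysis.** The full analysis set (FAS) decides the conclusion and is described as based on intention to treat. Its membership rule is "Patients who participate in randomization and receive at least one treatment will be included in the analysis". LOCF supplies the missing primary values of FAS patients who do not complete the trial.

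**The concern.** Stopping needling or exercise is a treatment decision. Ending measurement is a decision about data. The SAE sentence merges the two, and no section of the article provides for VAS or ROM measurement after withdrawal.

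Some SAEs do prevent later measurement, death being the plain case. Others, such as a short admission for an unrelated illness, leave a patient able to mark a VAS ruler and have shoulder motion measured some weeks later. For those patients the rule itself creates the missing value, and an earlier value then stands in for week 12. This works against an analysis set meant to follow the intention-to-treat principle, and it touches both primary outcomes.

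The rule is written in the text, so this is not a detail left to an analysis plan or to the full protocol.

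**Working it through.** **1. What LOCF would carry.** This uses the four assessments in Outcomes and assumes no exit assessment. If one is made, its value would be carried instead.

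| SAE occurs | Value carried to week 12 |
|---|---|
| During the 3 treatment weeks | Baseline (change of 0) |
| Follow-up weeks 1 to 4 | End of treatment |
| Follow-up weeks 5 to 12 | Week 4 |

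For an SAE before half of the sessions, criterion (4) of Patient dropouts may leave the patient out of the efficacy analysis, whereas the FAS rule needs only one treatment. The later values are lost either way.

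**2. Inputs.**
- From Sample size estimation: 36 patients per group, 108 in total. Mean VAS falls are 5.2 (SD 1.06) for stuck-moving needle (A), 4.7 (SD 1) for common acupuncture (B) and 3.5 (SD 1) for exercise (C). The A-B difference is 5.2 - 4.7 = 0.5.
- Assumed, because the article gives no figures: an SAE rate of 1% to 3%, a constant rate over the 3 + 12 = 15 weeks, and a carried value 1 to 2 VAS points off for an SAE in follow-up.

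**3. Number of patients.** 108 × 0.01 = 1.08 and 108 × 0.03 = 3.24.

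| Period | Share | Patients, all groups |
|---|---|---|
| Treatment | 3/15 = 20% | 0.22 to 0.65 |
| Follow-up weeks 1 to 4 | 4/15 = 27% | 0.29 to 0.86 |
| Follow-up weeks 5 to 12 | 8/15 = 53% | 0.58 to 1.73 |

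**4. Expected shift per group, follow-up SAEs.** The two follow-up rows hold 80% of the events: 1.08 × 0.8 = 0.86 to 3.24 × 0.8 = 2.59 patients. Spread over three groups, that is 0.29 to 0.86 per group. The expected shift in a group mean runs from 0.29 × 1/36 = 0.01 to 0.86 × 2/36 = 0.05 points. Where groups shift in the same direction, much of this cancels in the A-B difference.

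**5. One affected patient in one group, none in the other.** The shift is 1/36 = 0.028 to 2/36 = 0.056, which is 6% to 11% of 0.5. This is the unopposed case and not the expected one.

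**6. Treatment-phase SAE in group A.** Carrying baseline forward moves the group A mean by 5.2/36 = 0.144, or 29% of 0.5. The chance of at least one such patient in group A is 1 - (1 - 0.2 × rate)^36, which is 7.0% at a rate of 1% and 19.5% at 3%.

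**7. Effect on the planned test.** In 100,000 simulated trials with 36 per group and the means and SDs above, power of the three-group ANOVA at α = 0.05 was above 99.9% in each of four settings: no affected patient, one group A change 1 point worse, one 2 points worse, and one set to 0.

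**The case against.** The strongest objection is materiality. No SAE rate, timing or error in the carried value is given, so every size above is assumed. The planned ANOVA does not move, and the 6% to 11% figures arise only if the affected patient has no counterpart in the other group. All of this stands, and it sets the priority.

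A reader might infer that withdrawal after session 9 protects no one. The document does not support that. Pressure pain tolerance testing (PTT) raises the pressure until the patient finds it intolerable, and ROM is measured in five directions; someone recently admitted or operated on may fairly be spared these. The Intervention section also prohibits painkillers and physical therapy, and leaving the trial lifts any such restriction still in force. The remedy therefore has to cover both points.

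A reader might also infer that Patient dropouts contradicts the SAE rule. It does not. Criterion (1) also ends participation; it differs in being worded as investigator discretion and in naming serious reactions or critical illness rather than any SAE. That wording suggests practice may be less automatic than the SAE sentence reads, but it does not separate treatment from assessment.

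Two further objections hold in part. An exit visit may be described in the full protocol, which would change the value carried. VAS measured after an SAE may also reflect analgesics the trial otherwise prohibits, so keeping those values is a choice about what is being estimated as well as a recovery of data. An ITT-based FAS favours keeping them, with the rescue treatment recorded.

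**Conclusion.** The point holds as a low-priority improvement. As written, every SAE patient becomes a withdrawn subject whatever the cause or timing, and LOCF then replaces primary values that could in some cases still be measured.

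The effect is probably small: about 1 to 3 of 108 patients at an assumed SAE rate of 1% to 3%, partly balanced across groups, with the three-group ANOVA essentially unchanged. A reader might infer that the rule threatens the trial's conclusion or biases it towards one group. The document supports neither, since it gives no SAE rate and no reason to expect SAEs mainly in one group.

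How often a patient can still be assessed after an SAE is a judgement. LOCF for other non-completers, and the mismatch between the half-treatment and one-treatment inclusion rules, are separate matters and add no weight here.

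**What to change.** Replace the SAE sentence in Adverse events, and align criterion (1) of Patient dropouts, along these lines:

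- After an SAE, the remaining study sessions stop if the event is judged related to study treatment or makes further sessions unsafe. The SAE does not by itself withdraw the patient.
- The scheduled VAS and ROM assessments continue to week 12 unless the patient withdraws consent or cannot be assessed.
- Pressure pain threshold and tolerance testing (PPT and PTT), or any ROM direction, may be omitted if the investigator judges it unsuitable.
- Otherwise prohibited treatments needed for the SAE are allowed and recorded.
- LOCF applies only to values that could not be collected.

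The cost is a short amendment plus the notifications listed under Protocol amendments (fund regulator, participants, registries, journals), which apply because Trial status reports the first enrolment on 02 Jan. 2020. Each affected patient attends up to three assessments that are already scheduled, and the sample size does not change. The downside is that some later VAS values will be measured under rescue treatment.

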### Safety evaluation

The project will evaluate the safety of vital signs and the incidence of adverse acupuncture reactions.
Vital signs: Post-treatment respiration, heart rate, blood pressure, and body temperature.Incidence of adverse events: Adverse events will be referred as any unintended symptoms, signs, or health conditions that occurred after the start of the study. However, adverse events will not have a relationship with the treatment of this study. Adverse events include dizziness, hematoma, bleeding, infection, and abnormal pain at the treatment site. The number of adverse reactions will be counted at the end of the study, divided by the total number of each group, and the analysis will be carried out for the adverse events.Compliance analysis: The patient’s compliance with the treatment will be counted by the number of treatments. The formula is as follows: treatment compliance = the number of treatments the patient has received/the number of treatments the patient should receive × 100%.

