### Confidentiality

This study follows the ethical principles set out in the “Helsinki Declaration” and the various laws and regulations related to clinical research in China. Patients may receive acupuncture treatments such as trigger points during the study. Moreover, patients will receive free color Doppler ultrasound, muscle strength measurement, pain threshold measurement, infrared thermography, and various evaluation tests. Some patients may experience fainting, pain, bleeding, hematoma, or infection during acupuncture treatment. When such circumstance will arise, the patient will be handled properly and recorded in a timely manner.

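### The safety section says adverse events are unrelated to treatment, against its own list of needling harms, and it counts adverse reactions where the planned test compares adverse events

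*Protocol article*

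**What the plan says.** The Safety evaluation section of the protocol article opens with its purpose: "The project will evaluate the safety of vital signs and the incidence of adverse acupuncture reactions". It then gives a broad definition: "Adverse events will be referred as any unintended symptoms, signs, or health conditions that occurred after the start of the study". The next sentence restricts it: "However, adverse events will not have a relationship with the treatment of this study". The one after that gives examples: "Adverse events include dizziness, hematoma, bleeding, infection, and abnormal pain at the treatment site". The rate is then specified: "The number of adverse reactions will be counted at the end of the study, divided by the total number of each group".

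Three other sections bear on the point.

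- **Adverse events** sets the scope of recording: "All adverse events that will occur during the study will be recorded". Its paragraph on serious events names, among the items to write down, "the final outcome, the relationship with acupuncture treatment, the details of the treatment".
- **Confidentiality** warns: "Some patients may experience fainting, pain, bleeding, hematoma, or infection during acupuncture treatment".
- **Statistical analysis** compares the incidence of adverse events between the three groups by chi-square and says that the events will be listed. Tests are two-sided at 0.05.

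Group C receives exercise only. Groups A and B receive needling plus the same exercise.

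**The concern.** Two faults in the text affect what is counted as the safety result.

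First, the restricting sentence cannot stand beside its neighbours. It follows a definition that takes in every unintended event and precedes a list of events typical of needling. If the sentence is applied as written, an event judged to be caused by the needle is not an adverse event, and the experimental technique's own harms leave the comparison. Safety of the stuck-moving needle is a stated aim in both the Abstract and the Discussion.

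Second, the section changes its term between purpose, definition and count: acupuncture reactions, then adverse events, then adverse reactions. The planned test uses adverse events. If the count is of acupuncture reactions, group C is zero by construction and a three-group test tells the reader little. The stated rate also divides a number of reactions by a number of patients. That is an event count per patient, whereas a chi-square test of incidence needs patients with at least one event.

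**Working it through.** The plan states no adverse-event rate, safety sample size or safety power, so there is no figure to reproduce. The check is a comparison of the text, followed by an illustration on assumed counts.

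**Text side by side**

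| Place | What it implies for a needle-site haematoma |
|---|---|
| Safety evaluation, definition | Counted: an unintended event after study start |
| Safety evaluation, restricting sentence | Not counted if related to treatment |
| Safety evaluation, examples | Counted: haematoma is named |
| Safety evaluation, purpose and rate | Counted, as a reaction |
| Adverse events, scope | Recorded |
| Adverse events, serious events | Relationship with acupuncture noted, which would be pointless if events were unrelated by definition |
| Confidentiality | Recorded, and expected from acupuncture |
| Statistical analysis | Counted and listed as an adverse event |

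Only the restricting sentence excludes it. For an unrelated event, such as an intercurrent illness in group C, the split is different. The definition and the Statistical analysis section include it, while a count of reactions leaves it out. So the mismatch between reactions and events remains after the first sentence is mended.

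**Illustration (assumed counts, not document figures)**

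Inputs: n = 36 per group, from Sample size estimation. Assumed patients with a treatment-related event in A/B/C: 6/4/0. Assumed patients with an unrelated event: 3/3/3. No patient has both.

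For counts x with mean m over three equal groups, Pearson chi-square = Σ(x − m)² × [1/m + 1/(36 − m)], with 2 degrees of freedom and p = exp(−chi-square/2).

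- All events, 9/7/3: m = 6.333, Σ(x − m)² = 18.667, chi-square = 18.667 × (1/6.333 + 1/29.667) = 3.58, p = 0.167.
- Unrelated only (restricting sentence taken literally), 3/3/3: chi-square = 0, p = 1.00.
- Reactions only, 6/4/0: m = 3.333, Σ(x − m)² = 18.667, chi-square = 18.667 × (1/3.333 + 1/32.667) = 6.17, p = 0.046. The expected count of 3.3 per group is small, so this p-value is rough.

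A second set of assumptions uses related events in 15%, 10% and 0% and unrelated events in 5% of each group. The expected counts are 36 × 0.15 = 5.4, 36 × 0.10 = 3.6 and 0, and 36 × 0.05 = 1.8 per group.

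- All events, 7.2/5.4/1.8: chi-square = 15.12 × (1/4.8 + 1/31.2) = 3.64, p = 0.16.
- Unrelated only, 1.8/1.8/1.8: p = 1.00.
- Reactions only, 5.4/3.6/0: chi-square = 15.12 × (1/3 + 1/33) = 5.50, p = 0.064.

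In a wider set of cases, related counts ran from 4/3/0 to 10/6/1, with unrelated counts of 3/3/3 or 2/3/4. There p ran from 0.046 to 0.75 for all events, from 0.70 to 1.00 for unrelated only, and from 0.014 to 0.14 for reactions only.

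**The case against.** The strongest reply is that no sensible site would apply the restricting sentence. A broad definition followed by *however* most naturally leads to *need not have a relationship*, so the sentence looks like a drafting or translation slip. Every other statement points the same way: all events are recorded, haematoma and bleeding are named, and the trial's events are listed. Counting happens at the end of the study, so the wording can be put right before analysis. Most of this stands. A reader might infer that needling harms will go unrecorded, and the documents do not support that.

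It can also be said that reactions and events are used loosely as one thing. The item in question is titled as the incidence of adverse events, and the sentence that counts reactions ends by analysing adverse events. That is a fair reading of intent, but the numerator as written is still not the quantity tested.

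Two stronger inferences fail:

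- **Different safety conclusions from the same data.** The rates are invented. With the 15%, 10% and 0% assumptions no event set reaches 0.05, and the result crosses that line only under other assumed counts.
- **No place to record an event caused by exercise.** The article names a relationship item only for acupuncture and only for serious events, but it presents that list as what the record may include. The case report form and full protocol are not shown, so a missing exercise item cannot be established.

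**Conclusion.** The point holds as an internal contradiction with a second, separate mismatch. The restricting sentence is wrong as written. It conflicts with the sentences on either side of it, with the Confidentiality section's account of needling harms, and with the relationship record for serious events. Followed literally, it would take needling harms out of the safety result. If it is read as a slip, that consequence goes, but the sentence still needs correcting. The second fault does not depend on that reading: the rate counts reactions over patients, while the test compares adverse events in three groups, one of which cannot have an acupuncture reaction.

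The size cannot be stated from the documents. The illustration shows only that the choice of event set can move the planned test across 0.05 under some assumptions and not under others. It rests on 36 patients per group, on one event type per patient, and on event counts that are assumed throughout. Efficacy outcomes and randomisation are not affected.

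**What to change.** 1. In Safety evaluation, replace the restricting sentence so that the definition reads as any unintended event *whether or not related to the study treatment*. Keep the existing onset, after the start of the study.
2. In the same section, replace both the acupuncture reactions in the opening sentence and the number of adverse reactions in the rate with *the number of patients with at least one adverse event, related or not*. Name this in Statistical analysis as the quantity compared by chi-square across the three groups.
3. Define adverse reactions as the treatment-related subset, and report needling-related reactions descriptively for groups A and B only. This needs a relationship judgement for every event; if the case report form already holds one, nothing is added.

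The cost is a few sentences and, at most, minor form work, with no extra visits. Because the first participant was already enrolled when the article was written, the change should go through the route given under Protocol amendments and be settled before the safety data are counted.

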### Sample size estimation

According to the previous researches, the difference between the VAS score before and after treatment in the general acupuncture group was 4.7, with a standard deviation of 1, whereas the difference in VAS score before and after treatment in the functional exercise group was 3.5, with a standard deviation of 1 [14]. In combination with the pilot experimental results from this study, the VAS score before and after treatment of frozen shoulder patients with stuck-moving needle acupuncture dropped by 5.2 and the standard deviation was 1.06. This study was a prospective study with three groups and the sample size as 1:1:1. The sample size was calculated using *F*-test in software SAS 9.4, and we used single-factor analysis of variance to calculate the sample size. The test level was set at *α* = 0.05, β = 0.1, and the test efficiency was set at 1 − *β* = 0.9. The results showed that the test power was 0.931, and the number of samples in each group was not less than 30. By considering the problem of missing samples or losing to follow-up, the sample size will be increased by 20. This means that the minimum sample size of each group will be 36 patients, and finally, the total sample of the three groups will include cases not less than 108.

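### The one stated safety test compares three groups on mostly needle-related events, so it cannot show whether stuck-moving needling is less safe than common acupuncture

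*Protocol article*

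**What the plan says.** All references are to the protocol article.

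- **Test.** Statistical analysis: "the incidence of three groups of adverse events will be compared using a chi-square test". The same section sets two-sided testing ("All statistics will be performed by bilateral differential test") and the threshold ("value < 0.05 considered statistically significant"), and says that adverse events will be listed. It names no safety contrast between groups A and B.
- **Endpoint.** Safety evaluation opens with "the incidence of adverse acupuncture reactions". It then defines an adverse event as any unintended symptom, sign or condition arising after the study starts, related to treatment or not. Its examples are: "Adverse events include dizziness, hematoma, bleeding, infection, and abnormal pain at the treatment site". For the incidence, it divides the number of reactions by the number in the group.
- **Recording.** Adverse events says that all events are recorded. For serious events, the causality item is "the relationship with acupuncture treatment"; exercise is not mentioned.
- **Exposure.** According to Intervention and the three group sections, A and B receive needling plus exercise, and C receives exercise only.
- **Risks named elsewhere.** Confidentiality gives nearly the same list (fainting, pain, bleeding, hematoma, infection) as possible effects of acupuncture treatment.
- **Size.** Sample size estimation: "the minimum sample size of each group will be 36 patients", with "three groups and the sample size as 1:1:1".

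**The concern.** The Abstract and Discussion set out to evaluate the efficacy and safety of stuck-moving needling. The rationale describes it as a stronger stimulus than common acupuncture, and the Discussion makes common acupuncture the positive control. A reader will therefore want to know whether the new technique causes more harm than its active comparator.

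The stated test does not isolate that question. It pools two needled arms and one un-needled arm in a single test, on an endpoint whose examples are largely consequences of needling. The contrast between needling and no needling can produce a significant result by itself. The wording also shifts between acupuncture reactions and any adverse event, so it is unclear which of the two is tested. The answer determines how far C lies from A and B. Finally, exercise is given in all three arms, yet the causality item for serious events does not mention it.

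At stake is the safety conclusion, not the efficacy analysis.

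**Working it through.** **Plan's own figures.** No event rate and no power is stated for safety. The only power figure, 0.931 with 30 per group, belongs to the pain analysis and does not enter here (it does not reproduce: the stated means and SDs give more than 0.999 at 30 per group). The group size does reproduce: 30 × 1.2 = 36, reading the increase of 20 as 20%.

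**Inputs.** From the protocol: n = 36 per arm, three arms, threshold 0.05. Assumed: equal true rates in A and B of 10%, 15% or 20%, and a rate in C of 0%, 5% or 10%, where the rate is the proportion of patients with at least one event.

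**Statistic.** With x events in each arm and pooled proportion p̄ = (x_A + x_B + x_C)/(3n), X² = Σ(x_i − n·p̄)² / [n·p̄(1 − p̄)]. The test rejects above 5.99 (2 degrees of freedom).

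**One outcome by hand.** Take 6/36 in A, 6/36 in B and 0/36 in C. Then p̄ = 12/108 and n·p̄ = 4, so X² = (2² + 2² + 4²)/[4 × (1 − 12/108)] = 24/3.556 = 6.75, and P = exp(−6.75/2) = 0.034. The three-group test is significant although A and B are identical and their two-group statistic is 0.

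**Rejection probability.** Exact enumeration of three independent binomials, 36 per arm, A = B:

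| Rate in A and B | C = 0% | C = 5% | C = 10% | Direct A-versus-B test |
|---|---|---|---|---|
| 10% | 32% | 9% | 5% | 5.8% |
| 15% | 72% | 26% | 9% | 5.3% |
| 20% | 94% | 48% | 20% | 4.9% |

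- At lower rates with C = 0%, the three-group test rejects in 3% of trials (rate 2%) and 11% (rate 5%).
- With 30 per arm and C = 0%, the first column becomes 21%, 52% and 82%.
- With equal rates in all three arms, rejection is 4.6% (at 10%) and 5.2% (at 20%), so the test keeps its size.

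**When A and B do differ.** With A = 20%, B = 10% and C = 0%, the three-group test rejects in 81% of trials and the direct A-versus-B test in 22%. At equal A and B rates of 15% to 20% with C = 0%, the three-group test rejects in 72% to 94%. A significant result therefore looks much the same whether or not the techniques differ.

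**Sparse cells.** At rates of 10%, 10% and 0%, the expected number with events per cell is (3.6 + 3.6 + 0)/3 = 2.4, small for the chi-square approximation.

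**The case against.** The strongest reply has four parts.

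1. **The list is open.** The formal definition covers any unintended event, all events are recorded, and the examples are introduced as inclusions. Dizziness and pain at the treatment site can occur with the active and passive shoulder work in C. This stands. A reader might infer that C is bound to be almost free of events; the documents do not support that, and C = 0% is the extreme column of the table.

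2. **Rejection when A = B > C is correct.** The three-arm null is then false, and finding that needling adds harm to exercise alone is a legitimate result against a randomised control. This stands too. A reader might call the 32% to 94% false positives, or say that the test generally turns significant when the techniques are equally safe. Neither follows: the test keeps its size, and a high chance of rejection needs rates of about 15% to 20% in A and B with C near zero.

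3. **Pairwise safety contrasts may be in an analysis plan that is not shown.** This also stands, and their absence from the article is not in itself an error. The point rests on what is stated: a single three-group test, an endpoint with two meanings, and causality wording limited to acupuncture.

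4. **Exercise harm is not shown to be missed.** All events are recorded, assessors unaware of grouping evaluate safety (Quality control), and the causality item sits in a list of what the record may contain. A reader might infer under-ascertainment. The documents support only a risk that exercise-related events are not attributed to exercise.

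It is also true that no section says a significant three-group result will be read as A versus B. The protocol does, however, state no other safety test that would answer that question.

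**Conclusion.** The point holds in a limited form. The one stated safety test cannot separate the new technique from its active acupuncture comparator, because the needling contrast with C alone can make it significant. With A and B truly equal at 10% to 20%, it rejects in 32% to 94% of trials if C has no events, in 9% to 48% if C has 5%, and in 5% to 20% if C has 10%. A direct test rejects in about 5% to 6%. The size therefore depends heavily on rates that the protocol does not give. It also depends on whether the tested endpoint is acupuncture reactions or any adverse event, which the Safety evaluation section leaves unclear. Efficacy conclusions are not affected.

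**What to change.** 1. **Safety evaluation and Statistical analysis, all events.** Keep the any-event definition for all three arms, use it consistently, and describe all adverse events by arm.
2. **Same sections, needling reactions.** Add these as a separate endpoint, compared between A and B only. Report the proportion of patients with at least one event, rather than reactions divided by patients, and a confidence interval for the difference. Use an exact method, because counts will be small.
3. **Adverse events.** Extend the causality item for serious events to cover the relationship with acupuncture and with exercise, since every arm exercises.

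**Cost.** One extra safety table and changes to CRF wording. Treatment and sample size do not change. The A-versus-B comparison will be imprecise: power is about 22% for 20% versus 10%. As a rough guide, the 95% half-width at those rates is 1.96 × √(0.2 × 0.8/36 + 0.1 × 0.9/36) = 1.96 × 0.083 = 0.16, so a difference of 10 percentage points would carry an interval of about −6 to +26. A non-significant result should therefore not be reported as equal safety.
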